### Assessments

The design of MenDis-CHD is a monocentric cross-sectional mixed methods approach [25] comprising quantitative (primary and SHI data as secondary data) and qualitative research (interviews and focus groups).

#### Quantitative studies

##### Disease severity

We assess disease severity of CHD by ascertaining the reason of admission to hospitals, cardiology practices, and rehabilitation clinics, the actual therapy, secondary diagnoses, cardiovascular risk factors, left ventricular ejection fraction, NYHA (New York Heart Association) and actual medication. If applicable, we assess severity of cardiac events (e.g., heart attack), congestive heart failure, bypass-surgery, percutaneous coronary intervention, cardiac valve surgery, echocardiography, cardiac catheterization.

##### Clinical questionnaires

The *Hospital Anxiety and Depression Scale* (HADS; [26, 27]) will be used as a screening tool for MD. The HADS is a self-report questionnaire to assess symptoms of depression and anxiety. It contains 14 items, which can be rated on a 4-point Likert-scale. Depression and anxiety sub-scales can be extracted. An anxiety/depression score between 0 and seven is considered ‘negative,’ between eight and ten ‘sub-syndromal positive’ and between 11 and 21 ‘positive’ for depression and/or anxiety. The reliability for the anxiety scale is α = .80, for the depression scale α = .81. The retest-reliability within 2 weeks is α = .80 for the anxiety scale and α = .83 for the depression scale. The construct validity is between α = .06–.08. Cronbach’s Alpha of the HADS is 0.80, and the retest is indicated as α = .80 [28].

The sensitivity and specificity for case detection are around .80 for both scales [28]. HADS-screening will be defined as ‘positive’ if the score is greater or equal to eight. In this case, the *Structured Clinical Interview for DSM-IV* (SKID-I; [29]) will be conducted. The SKID-I is a semi-structured interview to assess psychiatric symptoms and disorders as defined in the DSM IV (*Diagnostic and Statistical Manual of Mental Disorders*; [30]). Lifetime and current diagnosis are assessed for the following disorders: [1] affective disorders, psychotic disorders, disorders through psychotropic substances, anxiety disorders, somatoform disorders, eating disorders and adjustment disorder. The test-retest reliability relevant for this study are within the range of α = .61–.76 for unipolar affective disorders and α = .65–.63 for anxiety disorders [31]. The sensitivity for affective disorders is .53 and for major depression .84. The specificity for affective disorders is .97 and for major depression .91 [32].

The *Demenz-Detection-Test* (DemTect; [33, 34]) will be used as a screening instrument to assess cognitive impairments. The DemTect contains five tests (1) a word list with immediate recall, (2) a number transcoding task, (3) a word fluency task, (4) a digit span reverse, and (5) a delayed recall of the word list. The total score of the DemTect gives an estimate whether the cognitive performance of the participant is normal for age (13–18 points), or whether mild cognitive impairment (MCI, 9–12 points) or dementia (8 points or below) should be suspected. In this study, we defined a DemTect score between 9 and 16 points as potentially indicative of cognitive impairments and thus will be regarded as ‘positive’. In case of a positive screening with the DemTect, the *Consortium to Establish a Registry for Alzheimer’s Disease* test battery (CERAD-Plus [35]) will be applied. If the DemTect score equals eight or is lower, the *Mini-Mental State Examination* (MMSE, 36) to detect significant cognitive deficits will be conducted. The test-retest reliability and the construct validity is above α = .80. The sensitivity is .97 and specificity is .93 [34]. The CERAD-Plus is a neuropsychologic test battery for the diagnostic of dementia [35]. It contains ten sub tests, which assess cognitive performance in different cognitive domains: (1) verbal fluency, (2) Boston naming test, (3) Mini-Mental Status Examination, (4) word list learning, (5) constructional praxis, (6) word list delayed recall, (7) word list recognition and discriminability, (8) constructional praxis delayed recall, (9) Trail Making Test A and B, and (10) phonematic fluency. The raw data will be z-standardized and adjusted for age, gender and education. If the z-score is between − 1.0 and − 1.5 SD, the cognitive performance is considered mildly impaired and below − 1.5 as severe impaired.

The *Mini-Mental Status Examination* [36] is a screening instrument to assess signs of dementia. The maximum is 30 points. The scores are interpreted as follows: 30–27 point: no evidence of cognitive impairment, 26–20 points: indicative of mild dementia, 19–10 points: indicative of moderate dementia, nine points and below: indicative of severe dementia.

The test-retest reliability is α = .89, and the construct validity is comparable to the construct validity of the DemTect [37]. The sensitivity is .88, and the specificity is .86 [38].

To estimate functional abilities in cognitively impaired patients, all participating relatives are asked to fill out the *Functional Activities Questionnaire* (FAQ; [39]). The FAQ contains ten items and rates the patient’s ability to perform daily activities. Participants rate each item on a 4-point Likert-scale ranging from 0 = ‘normal’ to 3 = ‘dependent’. The scores are added to a sum score of 30. If the score equals nine or is higher an impaired function in daily activities is indicated. The construct validity is α = .847, the sensitivity is α = .803 and the specificity is α = .870 [40].

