### Procedures

The University Hospital of Cologne (Department of Psychosomatics and Psychotherapy and Department of Psychiatry and Psychotherapy) is the only recruiting site. However, participants will be recruited in cardiology departments (University Hospital Cologne, Department of Internal medicine, Cardiology, Pneumology and Internal Intensive Care Medicine; Cologne-Merheim, clinics of the city of Cologne, Department of Cardiology, Rhythmology and Internal Intensive Care Medicine), patients from two cardiologic rehabilitation clinics (Clinic Roderbirken - Rehabilitation Centre for Heart and Circulatory Diseases; AmKaRe Cologne: out-patient cardiological rehabilitation centre) and from three cardiologic practices (Practice for Internal Medicine, Cardiology, Pneumology, Cologne, [name]; Practice for Cardiology Cologne, [name]; Practice for Cardiology Cologne, [name]). All patients screened for eligibility will be documented in a screening log. Patients who fulfill all inclusion and no exclusion criteria and provide written informed consent will be handed out the quantitative questionnaires and will be asked to participate in the qualitative interviews. If this screening with the HADS and/or the DemTect is positive, a second appointment will be arranged to perform the SKID-I and/or the CERADPlus. All participating researchers (SP and HM) were trained in applying the SKID-I and CERADPlus and are experienced in conducting the interviews with patients and research participants. The subsample of 20 participants, 20 relatives, and 20 physicians will be randomly contacted for a qualitative interview at a third time point. Furthermore, focus groups with 40 physicians will be randomly contacted.

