#### Qualitative

The qualitative module aims to analyze profoundly the patients’ needs, preferences, attitudes, and barriers regarding value-based care of CHD patients with comorbid MD. The overall research question of the qualitative module focuses on the trajectories of care and quality care of the CHD-patients, relatives, and physicians. In how far are their expectations met and which barriers are they facing?

Overall, outcomes of the patients’ data are: (1) prevalence of MD, (2) types of diagnostic procedures and treatment received, (3) quality of life, (4) satisfaction and short comings with respect to trajectories and quality of health care, and (5) expectations and needs with regard to health care (patient preferences). The outcomes will be analyzed separately for age groups and gender.

Main outcomes for the relatives’ data are: (1) frequency of contact with the health care system and provided care, (2) caregivers’ burden, (3) quality of life, (4) satisfaction with respect to trajectories and quality of health care, (5) patterns of perception about value, and (6) expectations and needs with regard to health care (preferences of relatives).

Main outcomes of the health care professionals’ are: (1) knowledge, attitudes, and experiences concerning guideline recommendations, (2) personal views and experiences regarding MD detection, treatment, and value for the patient, and (3) limitations and barriers in the health care system. Further, outcomes of the focus groups of the health care professionals are about obstacles about guideline adherence, diagnosis and treatment of MD in CHD.

In the SHI data the outcomes of interest are prevalence and incidence of MD diagnosis in CHD patients, documented diagnostics, and treatments (e.g., prevalence of psychotropic medication and/or psychotherapy), documented costs according to sectors of care, as well as treatment persistence, frequency and duration of hospital stay, sick leave certificates, early retirement and death.

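### SKID-I is given only after HADS >= 8, so the confirmed proportion is a lower bound for non-cognitive MD prevalence, about 20% low at the protocol's own HADS sensitivity

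*Protocol article*

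**What the plan says.** Under Clinical questionnaires, the Protocol article sets the gate: the HADS screen counts as positive "if the score is greater or equal to eight". It continues: "In this case, the *Structured Clinical Interview for DSM-IV* (SKID-I; [29]) will be conducted". Procedures repeats the sequence: if the HADS and/or DemTect screen "is positive, a second appointment will be arranged to perform the SKID-I and/or the CERADPlus". Clinical questionnaires pairs HADS with SKID-I and DemTect with CERAD-Plus. Neither section provides for interviewing HADS-negative patients, not even a random sample of them.

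On accuracy, the article says of HADS: "The sensitivity and specificity for case detection are around .80 for both scales". It gives neither the cut-off nor the reference standard behind that figure. Of SKID-I it says: "The sensitivity for affective disorders is .53 and for major depression .84", with specificities of .97 and .91 respectively.

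HADS is described as measuring depression and anxiety symptoms. SKID-I is to record both lifetime and current diagnoses, and its list also includes psychotic, substance-related, somatoform, eating and adjustment disorders.

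Outcomes (under the Qualitative subheading) lists "outcomes of the patients’ data are: (1) prevalence of MD". It does not say how that prevalence is to be computed.

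**The concern.** This is a two-stage design in which the second stage is never applied to first-stage negatives. If SKID-I-confirmed cases over all patients is reported as the prevalence, every true case with HADS below 8 is lost. The error runs downward and does not shrink with more patients. An ordinary confidence interval around the confirmed proportion describes sampling error only and gives no sign of it.

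The gate also controls diagnoses that it was not built to find. A patient with a remitted past depression, or with a substance-related disorder and few current symptoms of anxiety or depression, can score below 8 and never reach the interview.

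The study is descriptive, so the estimate is itself the product. An unseen analysis plan could apply an outside correction, but the study would hold no interview data on screen-negatives with which to support or check it.

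**Working it through.** **Inputs, all from the Protocol article.** N = 400 patients; expected prevalence 30–50%, for MD and MCI together (Patients); HADS sensitivity and specificity about .80 each; SKID-I sensitivity/specificity .84/.91 for major depression and .53/.97 for affective disorders (Clinical questionnaires).

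**The plan's own figure.** The article expects 130–200 patients with MD or MCI. 400 × .50 = 200 agrees. 400 × .30 = 120, whereas 130 corresponds to 32.5%. This small mismatch does not bear on the point. Because the 30–50% includes MCI, it serves below only as an illustrative range for non-cognitive MD. The relative loss does not depend on it.

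**Effect of the gate alone.** With SKID-I as the reference, confirmed proportion = p × Se(HADS). With Se = .80 and half-widths of 1.96 × √(q(1−q)/400), where q is the confirmed proportion:

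| True p | Confirmed | True cases not interviewed | 95% interval |
|---|---|---|---|
| 30% | .30 × .80 = 24% | 400 × .30 × .20 = 24 | about 19.8–28.2% |
| 40% | .40 × .80 = 32% | 400 × .40 × .20 = 32 | about 27.4–36.6% |
| 50% | .50 × .80 = 40% | 400 × .50 × .20 = 40 | about 35.2–44.8% |

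The relative loss is 1 − .80 = 20% in each row, and each interval lies below the true value.

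**If either subscale can open the gate.** If both scales could detect the same case independently, sensitivity would be 1 − .20 × .20 = .96. A true 40% then reads .40 × .96 = 38.4%, with a half-width of 4.8 points and an interval of about 33.6–43.2%, which includes 40%. The relative loss is 4%. Independence of two scales in one questionnaire is an optimistic assumption.

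**Assumed range for HADS sensitivity, .60 to .96.** A true 30% reads 18% to 28.8%; 40% reads 24% to 38.4%; 50% reads 30% to 48%.

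**SKID-I's own error, kept separate.** Confirmed proportion = p × .80 × Se(SKID) + (1 − p) × .20 × (1 − Sp(SKID)), with errors independent given true status. At p = 40%:

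- .84/.91: .40 × .672 + .60 × .20 × .09 = 28.0%. SKID-I for everyone would give .40 × .84 + .60 × .09 = 39.0%.
- .53/.97: .40 × .424 + .60 × .20 × .03 = 17.3%. SKID-I for everyone would give .40 × .53 + .60 × .03 = 23.0%.

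In the second case most of the fall from 40% arises in the interview and would remain if all 400 were interviewed. Confirmed false positives add only 1.1 and 0.4 points, so they do not offset the loss.

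**Other definition of the outcome.** Counting all HADS-positives as cases gives p × .80 + (1 − p) × .20, which is 38%, 44% and 50% at a true 30%, 40% and 50%. The choice of definition therefore moves the result as much as the gate does.

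**The case against.** The strongest reply is that the article never states the estimator. It does not say that HADS-negatives count as free of MD, or that the numerator is SKID-I-confirmed cases. That is correct, and the understatement applies only if the confirmed proportion is what gets reported. But the reply does not dispose of the point. The obvious alternative, HADS-positives, gives a materially different number, and under the described procedures no screen-negative patient can supply a diagnosis.

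A reader might infer more than the documents support:

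- **That a true 40% would be reported as 28% or 17%.** Those figures mix in SKID-I's own sensitivity, assume independent errors, and apply figures for major depression or affective disorders to all MD. They are not the effect of the gate.
- **That all MD depends on HADS.** The Abstract counts cognitive impairment among mental disorders, and that is found through DemTect and CERAD-Plus.
- **That the confidence interval must miss the truth.** It does at .80. At .96 with SKID-I as reference it does not.
- **That care-quality results are diluted in the same way.** The article does not name MD prevalence as their denominator, and proportions among confirmed cases are not lowered by missed cases as such.

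It is also fair to say that the study is exploratory and tests no hypothesis about prevalence. That limits the seriousness but does not remove the bias from a listed outcome. Finally, making a Rogan-Gladen or Bayesian corrected figure the main result would be hard to defend. The cited accuracies do not cover the full set of diagnoses, and the study cannot check them.

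**Conclusion.** The concern holds in a limited form. SKID-I-confirmed non-cognitive MD over all 400 patients is a lower bound, low by about 20% relative (6 to 10 percentage points at a true 30–50%). This rests on three assumptions: HADS sensitivity is .80 at the cut-off of 8, SKID-I is the reference, and the confirmed proportion is what is reported as prevalence. The loss falls to about 4% relative if either-subscale scoring reaches .96. For lifetime diagnoses and for the psychotic, substance-related, somatoform and eating disorders its size cannot be stated, because the article gives no HADS sensitivity for them. Cognitive impairment is outside the point, and SKID-I's own imperfect sensitivity is a separate matter.

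**What to change.** 1. Define the MD prevalence outcome as the proportion of all patients who are HADS-positive and SKID-I-confirmed. Report it as a lower bound for current depressive and anxiety disorders. Report cognitive impairment separately, by its own route.
2. Report lifetime diagnoses, and diagnoses other than affective and anxiety disorders, only among HADS-positive patients, with no population prevalence.
3. Add a sensitivity analysis, not the headline, that corrects the confirmed proportion over a stated range of HADS sensitivity, for example .60 to .96. With SKID-I as reference this is confirmed proportion ÷ sensitivity: an observed 32% would correspond to 53.3% at .60, 40% at .80 and 33.3% at .96.

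No visit or instrument changes. The cost is a less definite statement about prevalence and a little more analysis work.

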##### Health care questionnaires

Quantitative research in CHD patients, relatives and physicians will assess patients’ trajectories and quality of care, barriers to guideline-based care, health care preferences, quality of life, the presence of MD, disease severity and provided health care.

The three versions of the health care questionnaire comprise in total 158 items for patients, 147 items for relatives, and 76 items for physicians. Questions are for example: ‘Do you communicate with your physician (e.g., GP or cardiologist) about mental health issues?’

Furthermore, specific interventions and quality of health care in the enrolled patients are assessed by the *Patient Assessment of Care for Chronic Conditions* (PACIC; [41]). The PACIC contains 26 items, which are each rated on a 5-point Likert-scale ranging from 1 = ‘almost never’ to 5 = ‘almost always’. The higher the PACIC score, the better the patient-centeredness in health care from the patient’s point of view. Cronbach’s Alpha of the PACIC is 0.93, and the retest is indicated as α = .58 [41].

The *EURO-Quality of Life 5D* questionnaire (EQ-5D; [42]) measures the health-related quality of life in five dimensions (mobility, self-care, usual activities, pain/discomfort, anxiety/depression) with three items per dimension. The items are rated on a 3-point Likert scale from 1 = ‘no problems’ to 3 = ‘extreme problems.’ The higher the score, the worse is the health-related quality of life. The test-retest reliability for the five sub scales are α = .69, α = .77, α = .64, α = .48, and α = .61, respectively. All five sub scales are summed up in the life-quality index with a test-retest reliability of α = .75. The visual analog scale is a 20 cm vertical visual scale with endpoints ‘the best health condition you can imagine’ and ‘the worst health condition you can imagine.’ The visual analog scale can be used as a quantitative individual measure of health with a test-retest reliability of α = 92 [43].

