### Theoretical framework and research platform

MenDis-CHD is located in Cologne, Germany and is one of three current projects of the ‘Cologne Care Research and Development Network’ (CoRe-Net). Core-Net is funded by the Federal Ministry of Education and Research (BMBF), and the MenDis-CHD study protocol was subject to peer review by the funding body before approval. The value-based health care concept by M.E. Porter [20–22] forms the framework of CoRe-Net, which has the aim to create a data-driven learning environment employing research and practice to improve health and social care organizations by transforming them into a system that develops and delivers care with greater value. We define value-based health care as cost-consciously redesigning care processes and structures according to the needs of patients, which includes the two dimensions of patient-related and economic aspects. For further details about CoRe-Net see [23].

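### As worded, the EQ-5D index is an unweighted sum with an unclear item count and anxiety/depression as one fifth of it

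*Protocol article*

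**What the plan says.** The EQ-5D is described in the protocol article under Health care questionnaires. Four statements there bear on the score:

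- Structure: it "measures the health-related quality of life in five dimensions (mobility, self-care, usual activities, pain/discomfort, anxiety/depression) with three items per dimension".
- Coding: "The items are rated on a 3-point Likert scale from 1 = ‘no problems’ to 3 = ‘extreme problems".
- Direction, directly after the coding: "The higher the score, the worse is the health-related quality of life".
- Index, after the retest values of the sub scales: "All five sub scales are summed up in the life-quality index", for which a retest value of .75 is given.

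No weights, tariff or value set are named anywhere in the article. The visual analogue scale is described separately.

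Under Outcomes, quality of life is item (3) for patients and item (3) for relatives. Under Patients, the sample size is justified by the wish to make statistical comparisons in vulnerable subgroups, one of which is patients with MD and/or mild cognitive impairment.

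**The concern.** Read in sequence, these sentences describe adding the 1-to-3 codes. Higher-is-worse is the direction that such a sum has. Three things follow.

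1. **Equal weighting.** One step on self-care counts the same as one step on pain/discomfort, and the step from 1 to 2 counts the same as the step from 2 to 3. The result describes how many problems are reported and how severe they are. It cannot be placed beside preference-weighted EQ-5D index values from other work, although the name given to it invites that.
2. **Unclear range.** Three items per dimension does not fit with one three-level rating per dimension. The likely cause is that three response levels were taken for three items. The text does not allow the score range of a listed outcome to be recovered.
3. **Overlap with the grouping variable.** One of the five summed components is anxiety/depression. MD is found by HADS screening for anxiety and depression symptoms, followed by the SKID-I. Part of any difference in the sum between patients with and without MD is therefore built in.

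**Working it through.** The article gives no EQ-5D effect size, standard deviation or score range, so there is no stated figure to reproduce. The check is what the written rule yields.

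**Score range**

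- One rating per dimension: minimum 5 × 1 = 5, maximum 5 × 3 = 15.
- Three items per dimension: 5 × 3 = 15 items, minimum 15 × 1 = 15, maximum 15 × 3 = 45.

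**Profiles pooled by the sum (one rating per dimension)**

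There are 3^5 = 243 possible profiles. Enumerating them gives:

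| Sum | 5 | 6 | 7 | 8 | 9 | 10 | 11 | 12 | 13 | 14 | 15 |
|---|---|---|---|---|---|---|---|---|---|---|---|
| Profiles | 1 | 5 | 15 | 30 | 45 | 51 | 45 | 30 | 15 | 5 | 1 |

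The 243 profiles become 11 values. A sum of 10 covers 51 of them. In the order in which the dimensions are listed, 22222 (level 2 throughout) scores 2+2+2+2+2 = 10. So does 33211 (extreme problems on mobility and self-care, level 2 on usual activities, none on the other two): 3+3+2+1+1 = 10. Sums 9 to 11 cover 45 + 51 + 45 = 141 profiles, or 141/243 = 58%. These are shares of possible profiles, not of expected patients.

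**Share of anxiety/depression**

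- One rating per dimension: this dimension supplies 3 − 1 = 2 of the 15 − 5 = 10 points of range, or one fifth.
- Three items per dimension: it supplies 3 × 2 = 6 of 45 − 15 = 30 points, again one fifth.

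With one rating per dimension, if every patient with MD rated one level worse on anxiety/depression and the groups were identical on the other four dimensions, the mean sums would differ by exactly 1 point. The sum alone would not show where that point came from.

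**Does the quoted index reliability settle the reading?**

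The article gives retest values of .69, .77, .64, .48 and .61 for the sub scales and .75 for the index. Assume equal standard deviations and a common correlation ρ between dimensions (not given in the article). The reliability of an equal-weight sum is then 1 − Σ(1 − r)/(5 + 20ρ), with Σ(1 − r) = .31 + .23 + .36 + .52 + .39 = 1.81.

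| ρ | 5 + 20ρ | Reliability of plain sum |
|---|---|---|
| 0 | 5 | 1 − 1.81/5 = .64 |
| 0.1 | 7 | 1 − 1.81/7 = .74 |
| 0.2 | 9 | 1 − 1.81/9 = .80 |
| 0.3 | 11 | 1 − 1.81/11 = .84 |

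The stated .75 lies within this span, so it neither confirms nor excludes a plain sum.

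**The case against.** The strongest reply is that the article never calls the sum plain or unweighted. The index sentence stands in a run of published reliability figures and describes the instrument; it is not in the Statistical analysis section. The verb used may mean summarised. For the Functional Activities Questionnaire the authors say outright that item scores are added and give the maximum of 30 (ten items, 0 to 3); the EQ-5D index gets no such range. The direction sentence follows the item coding and may refer to the items, for which it is correct. The choice of value set is a detail that an article may leave to the full protocol or analysis plan.

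Much of this stands. The plain sum is the natural reading, not the only one. But the sentence would need correcting on either reading: if a sum is meant, it is mislabelled as a life-quality index without qualification; if a weighted index is meant, the text misdescribes it. An unshown plan that names a value set would leave the published description at odds with it. The conflict over the item count does not depend on this question.

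Two stronger readings are tempting and not supported:

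- A reader might infer that the planned setting of quality of life against cost fails. The article's framework does define value-based care by "the two dimensions of patient-related and economic aspects", but that is a framework statement. Costs are outcomes of the insurance claims data for 2011 to 2015, survey recruitment began in January 2018, and no person-level linkage or cost-utility analysis of the survey sample is described.
- A reader might infer that the visual analogue scale is wrongly specified because no numeric direction is given. Both endpoints are stated, and the numbering is detail that an article may leave out.

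**Conclusion.** The point holds as one of description and comparability. Read as written, the rule gives a level-sum score of 5 to 15 (or 15 to 45), with equal weights and steps, that is not comparable with preference-weighted EQ-5D index values. It carries anxiety/depression as one fifth of its range into comparisons of patients with and without MD.

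It would go too far to say that the sum measures nothing about quality of life: it is a usable descriptive severity score if it is named as one. Nor does the pooling of profiles show bias, since every sum score pools profiles.

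The conclusion rests on three assumptions: that the index sentence means addition, that no weights are applied elsewhere, and, for the profile counts, that there is one rating per dimension. That a comparable EQ-5D index needs a value set is general methods knowledge; the article does not say so. The study is exploratory, without a power calculation or confirmatory test, and quality of life is one of several outcomes, so no primary conclusion is at risk.

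**What to change.** - Correct the structure to five dimensions with one three-level rating each, if that is the form used, and name the EQ-5D version.
- Replace the index sentence: compute the index with a named national value set and state its direction. If a sum is truly intended, call it a level-sum score and give its range.
- Report the five dimensions separately for patients with and without MD, so that the contrast can be read without anxiety/depression.

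The cost is a few sentences, a standard scoring script and a few extra table rows. The raw responses are collected anyway and can be rescored at any time, so no new data are needed.
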